### Data collection and management

For each participant, anthropometric data (gender, age, body mass index (BMI)) and baseline characteristics such as GCS score, Acute Physiology and Chronic Health II (APACHE II) score, vital signs (blood pressure, heart rate, respiratory rate, blood oxygen saturation and temperature), and arterial blood gases (ABGs) will be recorded as long as the patients are in-hospital. Arterial blood oxygen saturation (SaO_2_), as well as end tidal carbon dioxide (PETCO_2_) if available, will be continuously recorded. In order not to cause unnecessary pain to patients, ABGs will be collected when deemed clinically necessary during follow-up, while other baseline characteristics will be recorded at set times.

We will also record incidence of the following for each enrolled patient:
PES, defined as a presence of an audible high-pitched sound with respirationOxygen therapy after extubation (e.g., nasal catheter, reservoir mask or venturi mask)Requiring a respiratory support, as defined by:
Presence of respiratory acidosis (an arterial pH of less than 7.35 with a partial pressure of arterial carbon dioxide of more than 45 mmHg)Clinical signs of increased respiratory effort (use of accessory muscles, intercostal retractions, or paradoxical motion of the abdomen)Respiratory rate > 30 breaths/min for two consecutive hoursHypoxemia (SaO_2_ of < 90% with an FiO_2_ > 50%)Reintubation secondary to PESAdverse effects due to corticosteroidsHospital length of stayHospital mortality.

Clinical data will be collected locally via the Research Electronic Data Capture (REDCap) system, an Internet-based electronic case report form (CRF). The research coordinators at each hospital will form a steering committee, which provides training and reviews study processes, to improve adherence to the protocol and resolve problems. In addition, they will regularly audit CRFs and contact responsible medical staff members every 3 months to ensure data quality and accuracy. All data use will be limited to study analysis only, and no individuals’ personal information will be published. Data confidentiality will be under the supervision of the study coordinators and the Ethics Committee of Peking Union Medical College Hospital.

### Statistical methods

The primary endpoint will be analyzed on an intention-to-treat basis, regardless of whether subjects complete their originally allocated treatment study protocol. Any reasons for protocol violations will be recorded and described. All *p* values will be two-tailed, and significance will be a *p* value < 0.05. Data will be presented as frequencies and percentages for categorical variables. Continuous variables will be expressed as means with standard deviations (when normally distributed) or as medians with interquartile ranges (for skewed distribution). Student’s *t* test (normal distribution) or Mann-Whitney *U* test (skewed distribution) will be used for group comparisons. Categorical variables will be compared using Pearson’s chi-squared test or Fisher’s exact test as appropriate. Statistical uncertainty will be expressed in terms of a relative risk and 95% confidence intervals.

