### Study endpoints

The primary endpoint is the occurrence of PES within the first 48 h after extubation. Secondary endpoints include oxygen therapy after extubation, respiratory support requirements, reintubation secondary to PES within 48 h after extubation, and adverse effects (glycemic change, gastrointestinal bleeding or neuropsychiatric events). Clinical assessments will be done at 5, 15, 30, and 60 min, and then at 3, 6, 12, 24, 36, and 48 h after extubation. Hospital length of stay and hospital mortality will also serve as secondary endpoints (see Fig. 2 for study flow chart).

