### Sample size calculation

We used a chi-squared statistical analysis of minimum sample size required to evaluate the effect of corticosteroids on our study outcomes. Cheng [10] showed that either a single or multiple doses of methylprednisolone 6 h before extubation reduced the incidence of PES compared to placebo (11.6%/7.1% vs 30.2%). Cheng [11] later reported that a single dose of methylprednisolone 4 h before extubation significantly reduced the incidence of PES from 39.4 to 15.8%. Other studies treating with prophylactic dexamethasone showed that it decreased the incidence of PES from 27.5–30.2 to 8.8–11.5% [12, 16]. We therefore anticipate an incidence of PES of 10% in the treatment group and 30% in the placebo group. With an 80% power to detect a difference and a two-sided alpha of 0.05, we anticipate needing 59 subjects in each group. Assuming a drop-out rate of 10%, we calculate a total minimum sample size of 132 subjects.

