### Randomization and blinding

As female sex has been reported to be an independent risk factor for stridor and extubation failure [5, 7, 10, 17, 18], a gender-stratified block randomization will be performed in a 1:1 ratio. Within each stratum, a random block size of four will be used. After completion of the pre-extubation assessment and obtaining written informed consent, participants will be randomly assigned to either the intervention group or the control group. Staff not assigned to patient therapy or assessment will be responsible for injecting the intervention; thus, both patients and therapists involved will be blinded to treatment allocation. All analyses will be performed on an intention-to-treat basis.

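### Randomisation is stratified by sex as a predictor of stridor, but the stated test of the primary endpoint ignores sex and is therefore slightly conservative if sex is prognostic

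*Protocol article*

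**What the plan says.** All references are to the protocol article.

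- **Randomization and blinding** gives the reason for stratifying, "As female sex has been reported to be an independent risk factor for stridor and extubation failure", and the scheme: "a gender-stratified block randomization will be performed in a 1:1 ratio". It adds: "Within each stratum, a random block size of four will be used".
- **Study endpoints** sets a binary primary outcome: "The primary endpoint is the occurrence of PES within the first 48 h after extubation".
- **Statistical methods** gives one rule for binary outcomes: "Categorical variables will be compared using Pearson’s chi-squared test or Fisher’s exact test as appropriate". On estimation it says: "Statistical uncertainty will be expressed in terms of a relative risk and 95% confidence intervals".
- **Sample size calculation** uses the same family of test, "We used a chi-squared statistical analysis of minimum sample size required", with these rates: "We therefore anticipate an incidence of PES of 10% in the treatment group and 30% in the placebo group". It arrives at 59 per group, and 132 in total after 10% drop-out.

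No section mentions an analysis stratified by or adjusted for sex.

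**The concern.** Blocking within sex fixes the proportion of women in each arm almost exactly. Between-sex differences in stridor risk then contribute almost nothing to the chance difference between arms. An unstratified chi-squared test still counts that between-sex component in its variance. When sex predicts the outcome, the assumed variance is therefore too large: the test rejects less often than 5% under no effect, the relative-risk interval is a little too wide, and some of the precision gained by stratifying is not used. The size of the problem depends on how strongly sex predicts stridor.

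**Working it through.** **1. The plan's own figure.** With rates of 30% and 10%, two-sided alpha 0.05 and 80% power, the unpooled formula gives

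n = (1.960 + 0.842)² × (0.3×0.7 + 0.1×0.9) / 0.2² = 58.87, rounded up to 59 per group.

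With 10% drop-out, 59/0.9 = 65.6, so 66 per group and 132 in total. The stated figures reproduce.

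**2. Assumptions.** The article gives no sex effect and no female share. I assume 40% women and a female-to-male odds ratio (OR) for stridor of 2, 3 or 5, with the overall placebo rate held at 30%. The implied rates in men and women are 24.1%/38.8% (OR 2), 20.7%/43.9% (OR 3) and 16.7%/50.0% (OR 5).

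**3. Type I error, closed form.** Under no effect, the chi-squared test uses p(1−p) = 0.3×0.7 = 0.21 per patient. With sex balanced, the variance that actually operates is the within-sex part, W = 0.6·p_m(1−p_m) + 0.4·p_f(1−p_f). The true type I error is approximately P(|Z| > 1.96/√(W/0.21)).

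| OR | W | √(W/0.21) | Effective cut-off | Type I error | Simulated, chi-squared | Simulated, CMH |
|---|---|---|---|---|---|---|
| 2 | 0.1098 + 0.0950 = 0.2048 | 0.987 | 1.985 | 4.7% | 4.8% | 5.0% |
| 3 | 0.0985 + 0.0985 = 0.1971 | 0.969 | 2.023 | 4.3% | 4.3% | 4.9% |
| 5 | 0.0833 + 0.1000 = 0.1833 | 0.934 | 2.098 | 3.6% | 3.7% | 5.0% |

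The simulated columns come from 200,000 trials per scenario at N=132, with blocks of four within sex. A separate simulation gave 4.6%, 4.3% and 3.5% for the unstratified test.

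**4. Power at 30% vs 10%.** Same simulation design, 40% women, unstratified chi-squared vs CMH without continuity correction:

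| OR | N=132 | Difference (points) | N=118 | Difference (points) |
|---|---|---|---|---|
| 1 | 84.0% vs 84.0% | 0.0 | 80.2% vs 79.4% | −0.9 |
| 2 | 84.1% vs 84.5% | +0.4 | 80.4% vs 80.1% | −0.3 |
| 3 | 84.6% vs 85.6% | +1.0 | 80.8% vs 81.3% | +0.5 |
| 5 | 85.1% vs 87.1% | +2.1 | 81.5% vs 83.2% | +1.8 |

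These runs hold the sex OR equal in both arms. Holding the treatment relative risk at 1/3 in both sexes instead gives −0.4, +0.3 and +1.5 points at N=118 for OR 2, 3 and 5. With 30% women and OR 5, the gain is 2.3 points at N=132 and 2.0 at N=118.

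**5. Interval width.** At the planned effect and N=132, the ratio of the stratified to the crude standard error of log RR is 0.994, 0.985 and 0.968 for OR 2, 3 and 5. The crude interval is thus 1/0.994 to 1/0.968, or 0.6% to 3.3%, wider on the log scale. Under no effect at 30% in both arms the ratios are 0.988, 0.969 and 0.935, or 1.2% to 6.9% wider.

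On the relative-risk scale, with 66 per arm at the planned rates, the crude standard error is √(0.7/(0.3×66) + 0.9/(0.1×66)) = 0.414. The interval around 0.33 is 0.15 to 0.75. Multiplying the standard error by 0.968 gives 0.15 to 0.73.

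**The case against.** The strongest reply is that the planned test is valid, the loss is small, and the detail may belong elsewhere.

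- **Size.** Much of this stands. A type I error below 5% is protection, not failure. At OR 2 the power difference is under half a point at N=132 and slightly favours the unstratified test at N=118. No conclusion is likely to turn on an upper limit of 0.73 rather than 0.75.
- **Coverage.** The stratified interval also over-covers at the planned effect (96.3% to 96.4%, against 96.5% to 97.0% for the crude interval). Most of the excess coverage is therefore not due to ignoring sex.
- **Consistency.** The unstratified test agrees with the chi-squared sizing, so the analysis matches its own power calculation. That is true, but it does not explain why the stratification factor is left out.
- **A matter for the SAP.** The methods paragraph is generic and does not name the primary endpoint. Still, stridor is binary and no other stated test can apply to it. The test is stated rather than left open, so a plan not shown that used a stratified test would have to depart from this text.

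Stronger readings are tempting. A reader might infer that the mismatch inflates false positives; the direction is the opposite. A reader might infer a serious loss of power from a very strong sex effect, such as placebo rates of 60% in women and 10% in men. That needs an odds ratio of (0.6/0.4)/(0.1/0.9) = 13.5, which nothing in the article supports. A reader might also worry that Fisher's exact test would cost much more power. At the planned rates, though, the smallest expected cell is 59 × 0.20 = 11.8, where Pearson's test would normally be chosen.

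**Conclusion.** The point holds as a minor matter of efficiency and calibration. The article balances a factor it regards as prognostic for the primary endpoint and then states a test and an interval that ignore it. With 40% women and a sex odds ratio of 2 to 5, both assumed, the unstratified test runs at about 4.8% to 3.5% instead of 5%. The interval at the planned effect is about 0.6% to 3% wider on the log scale. Power is about 0.4 to 2 points lower at N=132; at the planned evaluable 118 it ranges from no loss to about 1.5 points, or slightly more if the sex odds ratio rather than the treatment relative risk is constant.

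The documents do not support saying that the primary analysis is invalid, that power is lost whatever the sex effect, or that 132 patients are too few. In every scenario tabulated above, the planned chi-squared test keeps at least 80% power with 118 patients and stays at or below 5% type I error in the null scenarios simulated at N=132.

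**What to change.** Add one sentence to Statistical methods: the primary endpoint will be compared with a Cochran-Mantel-Haenszel test stratified by sex, and the effect reported as the Mantel-Haenszel relative risk with its 95% CI. A modified Poisson model adjusted for sex is an acceptable alternative. Keep the unstratified chi-squared test and crude relative risk as a supportive analysis.

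Sex is already recorded for every participant and the sample size does not change, so no extra data or patients are needed. The article's Trial status section describes recruitment as still to begin; the change should be prespecified before any unblinded data are seen. The one statistical cost is a loss of under 1 point of power at 118 patients if sex proves weakly prognostic or not prognostic at all (0.3 to 0.4 points at OR 2, 0.9 at OR 1).

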Ideally, patients at high risk for PES should be identified before extubation. The cuff-leak test (CLT), defined as the difference in the actual tidal volume before and after cuff deflation, has been proposed for this purpose [8, 9]. Previous studies described a cuff leak volume less than 110 ml or 24% of tidal volumes as insufficient [10–12], and evidence showed absent or insufficient cuff leak volume suggested an increased risk of PES and extubation failure [8]. Several studies showed the CLT has a good specificity but poor sensitivity, and the accuracy for predicting PES varied with different studies [13–15]. Moreover, the measured tidal volume could also be influenced by other factors such as system compliance or airflow resistance [13]. However, the CLT is still preferred as it has been showed to decrease the risk of PES and reintubation [9].

We conceived the present protocol in order to evaluate whether a single dose of methylprednisolone given over a set timeframe before extubation is effective in reducing the incidence of PES in patients who had been intubated on an emergency basis and were approaching extubation. We hope to answer this question through a multicenter, double-blind, randomized controlled trial.

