### Intervention, control, and observation groups

Once eligible patients successfully pass a spontaneous breathing trial (SBT), a CLT will be performed to evaluate their risk for developing PES. Patients who had a cuff-leak volume (CLV) less than 24% of vital volume will be included in the intervention arm, where they will be randomly allocated to either the corticosteroid group or the placebo group. The planned extubation will be implemented within 6 h after allocation. Patients in the corticosteroid group and placebo group will be treated with an intravenous injection of methylprednisolone 40 mg (corticosteroid) or an equivalent volume of isotonic saline (placebo) 4 h prior to extubation. Patients with a CLV > 24% of tidal volume will serve as a control group, where extubation will be performed within 2 h after CLT completion.

All other standard precautions or treatments will be implemented in all patients.

Precautions include gentle extubation to avoid laryngotracheal mucosal injury, strict endotracheal tube (EET) fixation to avoid repeated friction between the EET and laryngotracheal mucosa, and EET nursing to reduce contamination risk. Any treatments for PES will be applied in accordance with each patient’s condition, including oxygen therapy with inhaled corticosteroid for mild airway edema and intravenous administration of hydrocortisone (100 mg) for moderate airway edema. Non-invasive ventilation or re-intubation will be carried out as clinically indicated if the above treatments are ineffective.

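### The cuff-leak volume measured in every randomised patient serves only as an entry cut-off; prespecifying adjustment for it would be a low-cost improvement of uncertain size over a valid unadjusted test

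*Protocol article*

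**What the plan says.** The section on intervention, control and observation groups places a cuff-leak test after a passed spontaneous breathing trial, in order to judge stridor risk. It continues: "Patients who had a cuff-leak volume (CLV) less than 24% of vital volume will be included in the intervention arm". A CLV must therefore exist for each randomised patient before allocation.

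The Background gives the reason for selecting on it: "absent or insufficient cuff leak volume suggested an increased risk of PES and extubation failure". It also states the limits: "the CLT has a good specificity but poor sensitivity, and the accuracy for predicting PES varied with different studies", and adds that compliance and airflow resistance can affect the measured volume.

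After entry, CLV is not mentioned again in the design or analysis. Under Randomization and blinding the only stratifier is sex ("a gender-stratified block randomization will be performed in a 1:1 ratio"). The Data collection section does not name CLV among the recorded items, although its list of baseline characteristics is given as examples. Under Statistical methods the comparison of binary outcomes is "Categorical variables will be compared using Pearson’s chi-squared test or Fisher’s exact test as appropriate", with a relative risk and 95% confidence interval. No covariate is named.

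**The concern.** A baseline value that predicts the outcome can be used in the analysis of a randomised trial to reduce the variance of the treatment comparison. It also removes the effect of chance imbalance in that value between arms. Here the candidate is the very measurement the trial selects on, and obtaining it needs no extra procedure. With 59 to 66 patients per arm and no stratification on CLV, moderate chance imbalance is to be expected. The unadjusted 2×2 comparison leaves any risk differences between, say, absent leak and a leak just under 24% as noise. At stake are some precision in the one primary comparison and its robustness to an unlucky allocation. Adjusting only after an imbalance has been seen would be post hoc, so the choice has to be made in advance.

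**Working it through.** **The plan's own figure.** Inputs from Sample size calculation: PES risks of 10% on methylprednisolone and 30% on placebo; drop-out of 10%; and, for power and group size, "With an 80% power to detect a difference and a two-sided alpha of 0.05, we anticipate needing 59 subjects in each group". The stated total is 132.

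n per arm = [p₁(1−p₁) + p₀(1−p₀)] × (z₀.₉₇₅ + z₀.₈₀)² / (p₀−p₁)² = (0.09 + 0.21) × (1.960 + 0.842)² / 0.20² = 58.9, so 59. With 10% drop-out, 59 / 0.9 = 65.6, so 66 per arm and 132 in total. Both figures reproduce. (The pooled-variance formula would give 62, but in simulation the Pearson test reaches 80 to 81% power at 59 per arm.)

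**What adjustment could add.** The documents give no strength of association between CLV and PES below 24%. It is therefore an assumption here: CLV uniform over 0–24%, log-linear effect, odds ratio per SD lower CLV from 1.0 to 3.0, intercepts set so that the marginal risks stay at 10% and 30%.

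With 1:1 allocation and total N, N × variance of the risk difference is:
- unadjusted: 2 × (0.09 + 0.21) = 0.60
- adjusted: 2 × {E[π₁(1−π₁)] + E[π₀(1−π₀)]} + Var(π₁−π₀), where π₁ and π₀ are the risks given CLV in each arm.

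The variance ratio below is adjusted over unadjusted. The equivalent N is 118 × ratio, rounded up. Power comes from 10,000 simulated trials per row at 59 per arm (Monte Carlo standard error about 0.4 points), comparing Pearson chi-squared with the likelihood-ratio test for treatment in a logistic model with continuous CLV.

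| Odds ratio per SD (assumed) | AUC, placebo arm | Variance ratio | Equivalent N | Power, chi-squared | Power, adjusted |
|---|---|---|---|---|---|
| 1.0 | 0.50 | 1.00 | 118 | 80.4% | 80.3% |
| 1.25 | 0.56 | 0.99 | 118 | 80.6% | 80.6% |
| 1.5 | 0.61 | 0.98 | 116 | 80.0% | 80.8% |
| 2.0 | 0.69 | 0.94 | 111 | 80.9% | 83.4% |
| 2.5 | 0.74 | 0.90 | 106 | 80.4% | 84.4% |
| 3.0 | 0.77 | 0.86 | 102 | 80.4% | 85.8% |

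At 66 per arm the pairs are 83.8 and 84.3% (odds ratio 1.0), 84.1 and 87.0% (2.0), and 83.7 and 89.4% (3.0). A separate simulation at 59 per arm gave 80.8 and 80.7% (1.0), 80.1 and 80.9% (1.5), 80.1 and 82.1% (2.0), and 79.8 and 85.1% (3.0).

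**Type I error.** Two sets of simulations gave 5.3–5.7% adjusted against 5.0–5.5% unadjusted, and 5.5–6.0% against 5.3–5.8%.

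**Chance imbalance.** The difference in mean CLV between arms has standard error √(2/59) = 0.18 SD. In about 16% of trials, then, the methylprednisolone arm is at higher risk by more than 0.18 SD. In those trials power is 69% unadjusted and 83% adjusted at an odds ratio of 2.0, and 63% and 85% at 3.0. At 1.0 it is 81% and 80%. With imbalance the other way, unadjusted power rises to 90% (2.0) and 93% (3.0), while adjusted power stays within 81–85%.

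**Events for the model.** 59 × 0.10 + 59 × 0.30 = 5.9 + 17.7 = 23.6, about 24. The simulated models contain treatment and CLV but not sex.

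**The case against.** The strongest reply is that nothing here is wrong. Pearson's chi-squared test is valid in a 1:1 randomised trial, and it is the test the trial was sized on. Chance imbalance is already covered by its type I error. All of this stands.

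A reader might infer that the plan discards substantial precision, or that it ignores the main risk factor. The documents support neither. The Background contrasts patients with and without adequate leak; it states no gradient within 0–24%. All randomised patients lie below the cut-off, which restricts the range, and the reported poor sensitivity, variable accuracy and outside influences point towards a weak covariate. The factor the article calls independent is female sex, and that is stratified.

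At an odds ratio of 1.5 even the small gain is doubtful. Near 80% power, a size excess of 0.3 points is worth about 0.3 × 0.280 / (2 × 0.0584) ≈ 0.7 power points (normal densities at 0.842 and 1.960), nearly the whole simulated difference of 0.8.

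Adjustment is also not entirely free. CLV is not named among the recorded items, and its threshold is set once against vital volume and once against tidal volume.

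Finally, the test sentence covers all categorical variables and does not exclude an adjusted analysis in an analysis plan that is not shown. That limits how firmly one can say CLV is ignored. But the article does name a test and an effect measure, so an improvement on that stated choice can fairly be proposed.

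**Conclusion.** The point holds as a missed low-cost improvement. A CLV exists for each randomised patient before allocation, the protocol regards low leak as a risk marker, and the comparison it states is unadjusted. The stated test remains valid and the planned power is met.

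The benefit rests wholly on an assumed prognostic strength within the randomised range. It is negligible on average at an odds ratio per SD of 1.5 or less (variance down 0 to 2%, power up 0 to 1 point). At 2.0 to 3.0 it is modest (variance down about 6 to 14%, power up about 2.5 to 5.5 points at 59 per arm). If CLV is not prognostic, essentially nothing is lost. The case for prespecifying adjustment is this asymmetry, together with protection against an unlucky allocation if CLV does matter.

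**What to change.** Before any outcomes are seen:

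1. State the primary analysis of PES as logistic regression on treatment, baseline CLV (continuous) and sex, the stratification factor. Report a standardised (marginal) relative risk and risk difference with 95% confidence intervals.
2. Keep the chi-squared test as a supportive analysis.
3. Record the CLV value on the case report form.
4. Reconcile the vital-volume and tidal-volume wording of the threshold, so that the covariate has one definition. The entry criterion needs this in any case.

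The cost is slightly more analysis work, one more data item, and a very slight excess in the size of the likelihood-ratio test with about 24 expected events. No change to sample size or patient procedures is needed. Trial status puts the start of recruitment at around publication, so the change could be made before outcome data exist.
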